##### StayFitLonger training programme

The StayFitLonger programme will be accessible through the application *RestonsEnForme,* which will be available on a tablet (Galaxy Tab S2, Samsung) that will be provided to each participant. When launched, the main screen of the application provides access to different physical and cognitive activities (Fig. 1a) as well as other features listed below.

**Fig. 1 Fig1:**
[figure not shown]
Illustration of the different activities of the StayFitLonger training programme

The physical exercise activity (*Exercises*) will be based on the T&E home-based programme using the concept of self-efficacy and empowerment [39]. Participants will be invited to create a personalised 8-exercise programme (Fig. 1b). Those will be selected from 50 available exercises, which vary as function of themes (e.g., on a chair, with a pillow) and difficulty level (e.g., different body position or workload). Participants will try the exercises before including them in their programme. Exercices will only be included if judged as not too difficult by the participant. More details on the T&E programme can be found in [39]. During the intervention, participants will be allowed to add new exercises to their 8-exercise programme after a period of at least 3 weeks to introduce variety and increase challenge.

There will be four cognitive training activities which target problem solving, semantic memory, prospective memory, and divided attention. The *Quiz* activity will teach different strategies [49, 50] to learn new vocabulary and semantic repertoires (e.g., mushrooms, trees, flowers, dogs, etc.; Fig. 1c). Participants will choose first a repertoire of interest and will be asked to perform word-image associations related to the repertoire. Based on their level of proficiency in the selected repertoire, participants will then be offered different learning techniques: *completing* (relying on cues for help) or *copying/completing* (copying the word while using pure errorless learning and then completing while using encoding cues). Participants will continue to explore the repertoire through practice using an optimal number of cues to obtain the best performance while limiting the production of errors. This practice will be completed once participants reach at least 60% of correct responses without cues. Then, participants will be invited to a final evaluation without any help. Feedback will be provided with the option of continuing training using the repertoire or choosing another one. The *4 Images/1 Word* activity will train cognitive flexibility (Fig. 1d). Participants will be shown four images that are associated with an overarching concept and will be asked to find and write down the associated concept. Two types of cues will be provided to help them solve the task: number of letters in the target and some of the target letters mixed with distractors. The *Attention!* activity will train participants to vary their attentional priority in dual-tasks [40] while exploring a city on a two-wheel vehicle (Fig. 1e). The dual-task will involve detecting different targets in the environment (i.e., people, 4-wheel vehicles or buildings) by pressing a button on the screen (task A), and at the same time detecting sewer covers with foot taping (task B). The foot response will be recorded by a motion sensor attached to the waist or shoe. The activity will comprise 30 levels with a progressive increase in the degree of difficulty. Difficulty will be increased by manipulating the number of targets, the number of distractors and the speed of the vehicle driven by the player (i.e., bicycle, scooter, motorcycle) and by introducing a response contingency condition (if/then). Participants will complete first each task (detection of targets in the environment and detection of sewer covers) in focused attention. They will then be asked to combine the tasks with different priority levels during a series of trials: one trial in which they will devote 80% of their attention to task A and 20% of attention to task B, one with 20% on task A and 80% on task B, and one with 50% of their attention on each task. Each priority trial will last about 1 min and will be repeated twice in random order. The *Recall you* activity will be embedded into the physical exercises to train prospective memory [51] (Fig. 1f). On every 3 to 4 sessions, the *Exercises* activity will start with an instruction asking participants to complete a casual task (e.g., to get and drink a glass of water or to open a window, etc.) after a certain amount of time in the physical training. A timer will appear on the top left corner so that participants can track time while doing their exercises. For safety reasons, participants will be instructed to complete the exercise they are engaged in before performing the cognitive task.

In addition to the physical and cognitive activities, the StayFitLonger programme will include the following features:

A *Chat room* will provide a venue for participants to share views about topics of interest and tips for common real-life problems (Fig. 2a). Pre-established themes will be available (e.g., cooking, gardening, handiwork, etc.) and participants will have the opportunity to enrich this setting and create their own themes. When entering the chat room, a moderator message will inform participants to be respectful while chatting and to avoid revealing sensitive information (e.g., address, name, credit card information).

**Fig. 2 Fig2:**
[figure not shown]
Illustration of the unique features of the StayFitLonger training programme

*Creation of material*. Participants will be invited to create material for the *4 Images/1 Word* and *Quiz* activities. Once validated by the research team through a moderation platform, the material will be shared with all participants who will have the opportunity to use it for their own training and to rate the material created by other participants. This feature has been implemented to foster social interactions across participants.

*Psychoeducation*. From the application homepage, participants will have access to psychoeducational content (Fig. 2b) on different topics related to physical, psychological and cognitive health. Twenty-two topics will be available (e.g., divided attention improvement; stress regulation; fatigue management, etc.).

*Virtual coach*. A customisable virtual coach using verbal (but written) and non-verbal communication (Fig. 2c, d) will guide participants along the proposed exercises by giving them instructions, reminding them to practice a variety of available activities repeatedly, providing appropriate and timely feedback (through congruent facial expressions) on participant’s performances (e.g., encouraging messages) and rewarding assiduity, perseverance and performance with achievements and virtual credits (“physio-coins” and “cogni-coins”). Some achievements will unlock new icons, backgrounds and frames to modify the user interface, and by spending the coins obtained, it will be possible to get additional icons, background, frames and equipment to customise the virtual coach appearance (e.g., hat, glasses, etc.). These different functions of the virtual coach have been implemented to improve adherence by helping participants through a direct interlocutor (rather than neutral messages) and to keep them motivated [43].

##### Active control training programme

The active control programme will be similar in structure and layout to the StayFitLonger programme (Fig. 3a) and will include physical and cognitive exercises.

**Fig. 3 Fig3:**
[figure not shown]
Illustration of the different activities of the active control training programme

The physical exercise activity (*Exercises*) will be a computerised version of Helsana’s physical training programme (Fig. 3b). Helsana, a Swiss health insurance company, offers this programme in a booklet. The computerised version will include advice and tips to stay physically active (e.g., to go shopping by foot) and 12 exercises to train upper and lower extremity strength, mobility and balance. It will also provide information about which exercises to choose, the training frequency and precautionary measures to follow. This programme has been judged close to “standard care”, as it is similar to a large range of programmes and recommendations available to the general public. It will differ from the *Exercise* activity available on the StayFitLonger programme, as it only contains a limited number of exercises and does not benefit from interactive content (e.g., videos of exercises), self-management, personalization features, and rewards from the virtual coach.

The four cognitive activities provided in the active control programme will be commercially available leisure activities that do not target specific cognitive processes and do not teach cognitive strategies [52–56]. The *Crosswords* activity will include 219 puzzles with five different sizes (Fig. 3c). The *Sudoku* activity will include around 5000 puzzles with four levels of difficulty (Fig. 3d). The *Attention!* activity will be a maze arcade game inspired from Pac-Man in which participants eat dots in a maze while trying to avoid coloured ghosts (Fig. 3e). The *Countdown* activity will be embedded into the *Exercises* activity and triggered randomly every 3 to 4 days. It will require that participants count backward from 100 to 1 or recite the alphabet from Z to A while doing their exercise.

There will be no chat room, psycho-educational content or virtual coach included in the active control training programme.

##### Supervision during the intervention

Participants will receive a phone call and a home visit on week four and on week eight. Then, they will receive two phone calls (one from the physical activity instructor and one from the cognitive activity instructor) every four weeks. These will serve to identify and help participants to resolve difficulties with the programme, devices or exercises, and to obtain information about their health.

#### Outcome variables

##### Primary outcome

The primary outcome will be the performance on the TUG test [57]. In this test, the person will be sitting on a chair and will be asked to stand-up, walk three meters, turn around, walk back to the chair, and sit down. Time will be measured from the moment the person stands up until s/he sits down. Participants will perform the TUG twice providing two measures that will be averaged.

##### Secondary outcomes

Measures in four domains will be used as secondary outcomes (Table 2).

*Physical domain*. 1) Walking speed will be measured over a 20-m distance. Participants will be instructed to walk as quickly as possible without running and in a safe manner. Time will be measured in seconds using a smartwatch. The task will be carried out twice, and measures will be averaged. 2) Lower extremity strength will be measured with the Five Time Sit to Stand Test (FTSST) [58]. Participants will sit on a chair with arms folded across their chest and will be asked to stand up and sit as quickly as possible five times while keeping their arms folded. The task will be administered twice, and the two measures averaged. 3) In the Four Stage Balance Test (FSBT) [59], participants will be asked to perform four progressively more challenging positions and to hold each of them as long as they can for a maximum of 10 s (parallel, semi-tandem and tandem positions) or as long as possible (one-leg stance position). The test will be stopped if a participant fails at holding a given position. 4) A smartwatch (Huawei Watch 2) connected to two motion Physilog®5 sensors worn by participants will be used during the TUG and the 20-m Walking task to collect additional specific gait movement parameters (Table 2). These sensors are a standalone 7 degree-of-freedom MEMS inertial measurement unit with wireless synchronisation, including 3D accelerometer, 3D gyroscope, and a barometric pressure sensor. The system is non-invasive, as sensors will be directly strapped on right and left shoe/foot.

*Cognitive domain.* 1) Global cognition will be measured with the ZAVEN composite score [60, 61] computed by averaging z-scores from the following tests: delayed free recall of the California Verbal Learning Test (CVLT); delayed recall of the WMS-IV logical memory subtest [62]; number of correct symbols reported in the WAIS-IV digit symbol substitution test (DSST) [63]; and letter fluency of the verbal fluency task [64]. 2) An executive composite score will be computed by averaging z-scores from the following tests: letter fluency of the verbal fluency task; time to complete the Trail Making Test part B-A (TMT) [65]; interference index of the Victoria Stroop Test (VST) [66]; number of total visual and auditory omissions of the divided attention subtest (Test of Attention Performance 2.3.1; TAP [67];). 3) A memory composite score will be obtained by averaging z-scores from the delayed free recall score of the CVLT [68, 69] and the delayed recall of the logical memory task. 4) A processing speed composite score will be obtained by averaging z-scores from the following tests: time to complete the TMT part A; number of correct symbols reported in the DSST; time to complete the “naming condition” of the VST [70]. 5) Divided attention will be measured with a customized computerised task performed on a tablet [40]. Participants will be asked to deliver newspapers by pressing on a screen button while on a bicycle that moves forward automatically. At the same time, they will have to follow the road traffic regulation to ensure their safety (e.g., stopping when traffic lights go from green to red and avoiding animals crossing the road). The tasks will involve different distractors to vary participants’ attentional demand. Participants will be made aware that they should prioritize their safety as they would in real life. Each task will be done first in focused attention and then both tasks will be combined and performed using three levels of speed. The number of delivered items, reaction time, and errors will be recorded. 6) Prospective memory will be measured with two subtests of the Rivermead Behavioural Memory Test (RBMT-3) [71]. In the “belonging” subtest, participants will be instructed to remember asking for two personal belongings at the end of the session. In the “appointment” subtest, participants will be asked to remember asking two questions when an alarm rings 25 min later. 7) Concept elaboration will be assessed with the TAP flexibility sub-test, a “set shifting” computerised task [67] and the WAIS-IV Similarities subtest [63]. In the Similarities subtest, participants will be presented with pairs of words (e.g.: apple and peach) and will be asked how the two words are alike.

*Affective domain*. Mood will be assessed using the Hospital Anxiety and Depression Scale (HADS) [72]. Fear of falling will be measured with the Falls Efficacy Scale-International (FES-I) [73].

*Psychosocial domain.* Quality of life will be assessed with the 35-item Older People Quality of Life questionnaire (OPQOL 35) [74]. Cognition in everyday life will be measured with the self-reported Cognitive Function Instrument (CFI) [75] and Everyday Cognition scale (E-Cog) [76]. The CFI will include 14 questions to measure subjective concerns regarding cognition and activities of daily living over the last year. The E-Cog will measure how cognitive functions in different domains (everyday memory, language, visuospatial abilities, planning, organisation, divided attention) impact activities of daily living compared to 10 years ago. Participant’s expectation toward the efficacy of the training programme will be assessed with an ad-hoc 17-item questionnaire.

#### Statistical analyses

##### Sample size calculation

Given that our secondary analyses will stratify participants into two categories (robust and pre-frail), we determined our sample size to ensure that we have the capacity to test the hypotheses related to this stratification. This was done with a Marker Stratified Design using the following plan: marker-by-treatment interaction using separate test (see: http://www.bigted.org/NonAdaptiveDesigns/MarkerStratifiedDesigns.html). For pre-frail participants, it was estimated that 16 participants per group (StayFitLonger vs. active control) would be required to detect a significant difference of 3.22 s in the TUG test using a two-sided t-test (alpha = 0.05) based on the T&E pilot study. As data might not be normally distributed, a non-parametric test was required resulting in a sample size of about 18 participants per group. Considering a dropout rate of about 25% based on prior studies, a sample size of 24.5 pre-frail participants should be enrolled for each group. For robust older adults, a sample size of 23.5 participants per group would allow to detect a difference of 0.82 s on the TUG test using a two-sided t-test (alpha = 0.05) with a power of 80% based on the study by Uemura et al. [77]. By accounting for the non-normality of data (using a non-parametric test) and the dropout rate, we targeted recruiting 36 robust participants per group. Thus, a total sample of 122 participants was determined as sufficient to have the appropriate power based on sample size calculation. To have a balanced distribution in the three countries, the total N targeted for recruitment was set at 128 participants.

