##### Analysis of efficacy on primary and secondary outcomes

All statistical tests will be two-tailed and a *p* value < .05 will indicate statistical significance. Effect sizes will also be assessed. Standard descriptive statistics will be provided with means and standard deviation for demographics and baseline characteristics. Group comparisons will be made using t-tests for continuous variables and chi-square analyses for discrete variables.

The primary efficacy analysis will be done with a modified intention-to treat (mITT) approach. All participants will be included in the analyses and the characteristics of those who withdrew will be analysed, as well as the causes leading them to leave the study. A linear mixed model will be used to analyse the data, as it handles correlated data and unbalanced designs and are robust against missing values. The fixed effects will be Intervention (StayFitLonger vs. active control), Time (T0, T1) and their interaction. If the StayFitLonger training is more beneficial than the active control training, a significant interaction will be expected. In such case, the presence of a significant difference between T0 and T1 in each group will be evaluated, as well as group difference on change scores at post-training using the pre-training and control group as reference points. The same analysis will be used with primary and secondary outcomes. To examine the effect of frailty status on efficacy, participants will be stratified into robust and pre-frail seniors and data will be analyzed separately in these two populations using the same method described above.

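### The sample size allows for a non-parametric test that appears in no efficacy analysis, and the primary mixed model omits frailty, the stratification factor

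*Protocol article*

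**What the plan says.** Under Sample size calculation, each frailty stratum is sized on its own.

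- Pre-frail: "it was estimated that 16 participants per group (StayFitLonger vs. active control) would be required" for a 3.22 s difference, "using a two-sided t-test (alpha = 0.05) based on the T&E pilot study". Power is not given.
- Robust: "a sample size of 23.5 participants per group would allow to detect a difference of 0.82 s on the TUG test", with 80% power.

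The text continues: "As data might not be normally distributed, a non-parametric test was required". The pre-frail number goes from 16 to about 18 per group for that reason and to 24.5 after 25% dropout. The robust number goes to 36 per group after both allowances.

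Under Analysis of efficacy on primary and secondary outcomes: "A linear mixed model will be used to analyse the data". The fixed effects are intervention, time (T0, T1) and their interaction. The robust and pre-frail participants are then analysed separately by the same method. No rank-based efficacy test is named.

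Under Randomisation and blinding procedure, allocation is 1:1 within robust and pre-frail strata.

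**The concern.** Two adjacent sections each state a rule, and the rules differ. One sizes the trial for a non-parametric test. The other specifies a normal-theory model throughout, including the within-stratum fits for which the sizing was done. A reader cannot tell whether the inflation is a margin or the trace of an intended analysis.

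The same sizing figures suggest that TUG is far more variable in pre-frail than in robust participants, yet the pooled primary model is described without frailty. At stake are the precision of the primary comparison and how far the pooled result depends on the pre-frail stratum.

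**Working it through.** **Inputs.** From Sample size calculation: two-sided alpha 0.05; 3.22 s with 16 per group (pre-frail); 0.82 s with 23.5 per group and 80% power (robust); 25% dropout. The efficacy section agrees on the level: "All statistical tests will be two-tailed and a *p* value < .05 will indicate statistical significance". Assumed: 80% power for the pre-frail stratum, with 70% to 95% as the range. No SD is stated.

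**Step 1. Reproduce the enrolment.** The figures fit a 15% rank-test inflation followed by division by 1 − 0.25.

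- Pre-frail: 16 × 1.15 = 18.4; 18.4 / 0.75 = 24.5.
- Robust: 23.5 × 1.15 = 27.0; 27.0 / 0.75 = 36.0.
- Total: 2 × (24.5 + 36) = 121, or 122 when 24.5 is rounded up to 25.

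The plan's figures are reproduced. Dividing by the worst-case Wilcoxon efficiency of 0.864 instead gives 24.7 and 36.3, which also fits.

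**Step 2. Implied SDs.** By the normal approximation, SD = difference / [(1.960 + 0.842) × √(2/n)].

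- Pre-frail: 3.22 / (2.802 × 0.354) = 3.25 s; exact noncentral t, 3.15 s.
- Robust: 0.82 / (2.802 × 0.292) = 1.00 s; exact, 0.98 s.
- Variance ratio: 10.5 (approximate) or 10.3 (exact).

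If the unstated pre-frail power was 70%, 85%, 90% or 95%, the exact ratio is 13.1, 9.0, 7.7 or 6.2.

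**Step 3. What this means for a pooled comparison.** Take 18 pre-frail and 27 robust completers per arm (step 1 before dropout), and treat the implied SDs as SDs of change with one common variance.

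- Pooled SD = √(0.4 × 3.15² + 0.6 × 0.98²) = 2.13 s. SE = 2.13 × √(2/45) = 0.449 s.
- Uniform 0.82 s benefit: z = 0.82 / 0.449 = 1.83, power about 45%.
- Stratum SEs: 3.15 × √(2/18) = 1.05 s and 0.98 × √(2/27) = 0.267 s. The inverse-variance SE is 0.259 s, so z = 0.82 / 0.259 = 3.17 and power is about 89%.

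Simulation with normal data (40,000 trials per case) gives these rejection rates:

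| True benefit (pre-frail / robust) | Pooled t-test | Pooled rank test | Inverse-variance |
|---|---|---|---|
| none | 5.0% | 4.9% | 5.7% |
| 3.22 s / 0.82 s (planned) | 97% | 98% | 96% |
| 0.82 s / 0.82 s | 45% | 63% | 89% |
| 3.22 s / 0 s | 75% | 53% | 14% |

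**Step 4. Leaving frailty out.** In a two-time-point model the term that matters for change is frailty by time. Assume that the strata differ by 1.5 s in mean change whatever the arm; this figure is illustrative and not in the document. In simulation the unadjusted test then has type I error 3.9% and power 94.6% at the planned effects. With frailty in the model these become 4.9% and 97.6%. A van Elteren test used as a sensitivity analysis kept its level.

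**The case against.** A reader might infer that the primary analysis is a single-variance model of TUG in seconds that wastes the robust stratum and leaves the trial underpowered. The article does not support that. It states neither the residual structure nor the scale of TUG; these are usual defaults, and a full plan could set them otherwise.

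A reader might also take the text to say that TUG needs a rank test. It says only that the data might not be normal, so the inflation can stand as a conservative allowance.

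Other points that stand:

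- The sizing was openly done for the stratified secondary analyses. Those are separate fits, each with its own variance, so the variance gap affects only the pooled analysis.
- The SDs are back-solved from two different source studies, and the article does not say whether they describe change or a single visit.
- Low pooled power is not the general case. With 0.82 s in robust participants, pooled power reaches 80% once the pre-frail benefit d satisfies (0.4d + 0.6 × 0.82) / 0.449 = 2.80, that is d of about 1.9 s.
- Inverse-variance weighting is not a free gain. It puts about 94% of the weight on robust participants (1/0.267² against 1/1.05²), which changes what is estimated.
- Whether a log scale would equalise the variances depends on stratum mean TUG values that the document does not give.

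None of this removes the mismatch over the non-parametric test, or the absence of frailty from a list of fixed effects that the article does spell out.

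**Conclusion.** The sizing and efficacy sections need to be reconciled, and the primary model should carry the stratification factor. This concerns efficiency and clarity, not validity: with 1:1 allocation within strata the variance gap leaves type I error at 5.0%, and omitting frailty makes the test, if anything, conservative.

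The implied variance ratio is about 10 on the assumption of 80% pre-frail power, and 6 to 13 otherwise. Pooled power is about 97% at the planned effects and about 45% for a uniform 0.82 s benefit, if the implied SDs are SDs of change and the data are normal. The effect of skewness was not tested. Because the ranking of methods reverses with the effect pattern, the case is for fixing the choices in advance. It is not a case for making precision weighting or log TUG the primary analysis.

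**What to change.** 1. Add frailty and frailty-by-time to the fixed effects of the primary mixed model.
2. Pre-specify two sensitivity analyses: a frailty-stratified rank test (van Elteren) on change in TUG, and the mixed model with residual variance allowed to differ by frailty stratum. A log-TUG version is optional and need not be primary.
3. State under Sample size calculation that the rank-test inflation of roughly 15% is a margin and not the planned primary test.

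The cost is a few degrees of freedom and a little more analysis work. No new data or participants are needed.
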